# Glossary of Abbreviations and Terms

CDM – Chronic Disease Management

CLD – Chronic Liver Disease

CLDQ – Chronic Liver Disease Questionnaire

CM – Case Management

FMC – Flinders Medical Centre

GP – General Practitioner

HCC – Hepatocellular Carcinoma

HCV – Hepatitis C Virus

HE – Hepatic Encephalopathy

LMH – Lyell McEwin Hospital

NAFLD – Non-alcoholic fatty liver disease

PIH – Partners In Health

QEH – Queen Elizabeth Hospital

RAH – Royal Adelaide Hospital

RCT – Randomised Controlled Trial

SBP – Spontaneous Bacterial Peritonitis

SCGH – Sir Charles Gairdner Hospital

# Planned Timeline

April 2020

April 2022

September 2018

First patient randomised

Last patient randomised

EOT

Intervention starts

Intervention ends

Each patient will receive 24 months of intervention will be different for each patient.

# Background

**Cirrhosis and chronic liver failure**

A variety of insults to the liver can lead to progressive fibrosis and cirrhosis. The most common causes in Australia include; alcohol abuse, chronic hepatitis C (HCV) infection, and non-alcoholic fatty liver disease (NAFLD). Ongoing injury to a cirrhotic liver may result in decompensation of liver functions or chronic liver failure (CLD). CLD is manifested by complications such as; ascites, variceal bleeding, encephalopathy, sepsis (most commonly spontaneous bacterial peritonitis) and renal dysfunction, protein calorie malnutrition and hepatocellular carcinoma (HCC). The prognosis following the onset of CLD is poor. Patients with early CLD (Child Pugh class B) have a 2-year survival of only 60% and this falls to 35% in advanced CLD (Child Pugh class C)([1](#_ENREF_1)).

**Prevalence and economic impacts of CLD in Australia**

Cirrhosis and CLD have a high prevalence and significant economic impacts in Australia. In Australia it is estimated that 6.17 million people are affected by liver diseases which result in 7,266 deaths in 2012 ([2](#_ENREF_2)). The direct health expenditure (hospital admissions, out of hospital medical services, prescription pharmaceuticals) associated with liver disease was estimated at $386.2 million per annum in 2012. The total financial cost of liver disease in 2012 including direct health costs, productivity impacts, informal carer costs, loss of taxation revenues and disability adjusted life years has been estimated at $50.7 billion dollars ([2](#_ENREF_2)). These high costs reflect the significant disability, morbidity and mortality associated with CLD. These costs are 40% more than those associated with type 2 diabetes and represent 39% of the annual cost of cardiovascular disease, one of the most costly conditions in Australia.

These costs are likely to increase substantially in the future reflecting a steady rise in the prevalence of CLD in Australia. Evidence for this increase comes from a variety of sources. Firstly, deaths from cirrhosis and CLD in Australia have increased 20% between the years 1999 and 2008 ([3](#_ENREF_3)). An analysis of ICD-10 codes for CLD diagnoses shows a national increase of 25% in hospital admissions for CLD between 2004/5 to 2007/8 ([4](#_ENREF_4)). The reasons for this increase are likely to be associated with the growing epidemics of alcohol abuse, hepatitis C and obesity within Australian communities. Three available National Health surveys indicate that the proportion of Australians drinking at hazardous levels has increased from 8.2% to 13.4% ([5](#_ENREF_5)). Increased per capita alcohol consumption ([6](#_ENREF_6)) and increased hospital admissions for alcoholic liver disease ([7](#_ENREF_7)) provide further evidence of increasing patterns of alcohol use in Australia. In addition, despite the arrival of highly effective antiviral therapy for HCV it is anticipated that without substantial increases in treatment uptake a three-fold increase in numbers of patients cirrhosis, HCC and liver-related death by 2030 ([8](#_ENREF_8)). The rising rates of obesity (from 38% of Australians to 54% in the last available Australian Bureau of Statistics survey ([9](#_ENREF_9)), is another important current driver of the increasing numbers of patients entering cirrhosis and CLD.

**Problems with the current management models of CLD**

A number of effective, evidence-based treatments have been shown to improve survival in CLD patients. These include disease specific therapies such as; alcohol abstinence for alcoholic liver disease, antiviral therapy for viral hepatitis and immunosuppressive therapy for autoimmune hepatitis. In addition a number of evidence based therapies can improve survival for end stage manifestations of CLD including; antibiotic prophylaxis for patients with ascites, primary prophylaxis using beta blockers or endoscopic variceal ligation for high risk varices, surveillance for HCC in at risk patients and aggressive nutrition of severely malnourished cirrhotic patients. Large volume paracentesis, sodium restriction and diuretics for ascites can improve patient quality of life and reduce hospitalization ([10](#_ENREF_10)) as can available treatments (lactulose and rifaximin) for hepatic encephalopathy ([11](#_ENREF_11)). For patients who fail to improve despite medical therapies, liver transplantation can restore normal liver function and is associated with an overall 80% 5-year survival in Australia and New Zealand.

However, despite the availability of effective therapies, available data suggests the delivery of such care to CLD patients is suboptimal. In routine practice poor rates of variceal screening and prophylaxis of high risk varices ([12](#_ENREF_12)), poor adherence to guidelines for hepatocellular carcinoma surveillance ([13](#_ENREF_13), [14](#_ENREF_14)) and poor adherence to ascites management guidelines ([15](#_ENREF_15)) have been observed by multiple investigators. Suboptimal care is a likely contributor to frequent, prolonged, costly and often preventable readmissions that characterize this disorder ([16](#_ENREF_16)). The CLD-related readmission rates have been identified as 14 %, 37 % and 53 % at 1 week, 3 months and 6 months respectively by recent studies ([16](#_ENREF_16), [17](#_ENREF_17)), with an estimated 52 % of these readmissions judged as preventable by improved care. The reasons for inadequate care delivery in CLD patients appear complex and multi-factorial. The lack of hospital clinician focus on preventative care measures, absence of robust systems to improve patient follow up and monitoring following discharge, and poor integration of hospital and primary care team members are all likely contributing factors. Finally, poor engagement of patients in their own care and inadequate patient education is also likely to be of major importance.

**Chronic Disease Management Models**

Significant changes in the current model of care are required in order to make meaningful improvements in the management of this complex and challenging disease. A candidate model is the CDM model, first articulated by Wagner et al. in 1996 ([18](#_ENREF_18)) and subsequently developed by other groups. The key components of CDM are; self-management support, delivery system design, decision support and clinical information systems, community linkages and support from health care organizations. CDM approaches have produced positive outcomes in a number of non-liver chronic disease settings including; heart failure, ischemic heart disease, chronic obstructive lung disease and diabetes ([19](#_ENREF_19)). Three meta-analyses of over 30 randomized controlled trials (RCTs) using a variety of CDM approaches in heart failure have shown similar results. These studies demonstrated a 30% to 42% reduction of heart failure related admissions and a 12% to 27% reduction in all cause admissions, together with a mortality reduction of 18% to 25 % relative to usual care ([20-22](#_ENREF_20)). These clinical improvements were also associated with significant cost savings in 15 of the 18 trials where financial outcomes were evaluated ([20](#_ENREF_20)). As a result of these studies CDM style approaches are now the standard of care in heart failure and have been given a class 1 recommendation in practice guidelines ([23](#_ENREF_23)). Similar findings have been reported for chronic obstructive lung disease with a meta-analysis of RCTs of CDM programs demonstrating a 22% reduction in hospitalizations, 42% reduction in unscheduled emergency and outpatient visits, but no reductions in mortality ([24](#_ENREF_24)).

**Preliminary studies of CDM models in CLD**

CLD would appear to be a logical choice for CDM style interventions. It is characterized by frequent, lengthy and costly admissions and has effective but poorly implemented evidence-based treatment. However, it remains unclear if findings from other disease trials can be adapted to the unique challenges of CLD which include; high short term mortality, high rates of drug and alcohol addiction, frequently social disadvantage and marginalization from health care and multiple aetiologies and clinical presentations. The urgent need for RCTs has been highlighted by editorials in high impact gastroenterology journals ([25](#_ENREF_25), [26](#_ENREF_26)). However, the only RCT published to date has been a pilot trial performed by [name] et al ([27](#_ENREF_27)) and subsequently editorialized by high impact gastroenterology journals ([28](#_ENREF_28), [29](#_ENREF_29)). In this single centre trial of 60 patients a multifaceted CDM model was used during a 12 month period. The main components of this intervention were delivery system re-design (co-ordinated case-management, home visits, weekly telephone reviews, rapid access to care pathways) and increase self-management support (patient action plans, increased education and self-monitoring, medication blister packs).

The major findings of this pilot trial were:

- No reduction in the primary endpoint of liver-related occupied bed day rates in the intervention versus usual care arms (17.8 vs 11.0 bed days/person/year, incidence rate ratio=1.6, 95% CI=0.5-4.8, P=0.39), however a non-significant 21 % reduction in unplanned/emergency admissions
- Non-significant reduction in mortality in intervention arm (Hazard ratio 0.6, 95% CI=0.3-1.5, P=0.32)
- Significantly improved quality of life for intervention patients relative to baseline but no significant improvement relative to usual care group
- Significantly improved quality of care in intervention group for outpatient attendance and adherence to protocols for HCC screening, vaccination and bone density surveillance.
- Cost effectiveness was demonstrated in a subsequent analysis which showed the intervention was less expensive per patient by a mean of $ 57,000 per participant with a 96 % probability of cost effectiveness at a willingness to pay of $ 40,000 per death avoided ([30](#_ENREF_30)).

A further published trial investigating the effects of CDM/care co-ordination models in cirrhosis was a non-randomized study of 100 patients followed for 12 months ([31](#_ENREF_31)). This model consisted of a “care management check-up” whereby all investigations were performed and preventative treatments commenced during a day admission to a day hospital.

The chief findings of this study were:

- Significantly reduced mortality in the intervention group (23% versus 45.7%, p<0.025)
- Significantly reduced 30-day readmission in intervention group (15.4% vs. 42.4%, p=<0.01)
- Significantly lower cost per patient month in the intervention group (1479€ vs. 2816€, p<0.05)

A final non-randomized study by Tapper et al ([32](#_ENREF_32)) investigated prospectively the effects of an electronic discharge checklist on subsequent readmission rates in patients with cirrhosis. The electronic decision support significantly reduced readmissions by 40%, mainly driven by improved compliance with rifaximin and reduced encephalopathy related readmissions.

**Indication for proposed new trial**

Providing a firm evidence base for CDM models in cirrhosis is one of the key research priorities currently in gastroenterology due to the rising prevalence and costs of CLD and was a key recommendation of the recent report commissioned by the Gastroenterology Society of Australia ([2](#_ENREF_2)). Unfortunately the current evidence base for CDM models in CLD, described above, is inadequate to support the use of these models in CLD.

While the pilot study of [name] et al was an informative study, limitations of the study also limit its clinical usefulness. Firstly the study was designed to investigate feasibility of a future RCT and was not powered to investigate the most clinically relevant endpoints of patient mortality and cost effectiveness. Secondly the small sample size of the pilot trial left it susceptible to imbalance of disease aetiology between groups, with a higher proportion of alcoholic liver disease in the usual care group. A further concern was the trial setting in a single, tertiary care, transplant centre and high quality of care observed in the usual care group may have concealed benefits of the intervention that may have been revealed with a multiple site investigation. A requirement for hospital admission for trial entry may have also introduced a selection bias of terminal phase patients, too sick to benefit from the intervention The relatively short 12-month follow up of the trial may also not have captured the longer-term beneficial effects of the intervention. The unexpected trend towards increased hospitalization also suggests that CDM style interventions may have different effects in CLD compared with other chronic diseases with increased admissions of relatively sicker patients due to improved access to care. This phenomenon has previously been noted in primary health care settings treating patients with severe chronic diseases ([33](#_ENREF_33)).

Conclusions from the aforementioned “care management check-up” study ([31](#_ENREF_31)), while promising, are also limited by significant flaws in study design. Lack of randomization, lack of process measure measurement, unexpectedly high death rate in usual care group, use of adjusted rather than unadjusted analyses and failure to provide robust cost effectiveness data are all significant concerns that have been highlighted ([26](#_ENREF_26)). While the Tapper study ([32](#_ENREF_32)) also shows the potential of electronic decision support interventions conclusions and are also limited by its lack of randomization and generalizability is limited by the use of sophisticated electronic medical records and the study setting in an advanced quaternary care transplant unit.

In summary appropriately powered and designed trials of CDM in CLD with appropriate endpoints are an urgent and important research priority in gastroenterology to help provide definitive evidence concerning their effectiveness and cost effectiveness to both clinicians and funders of healthcare. The proposed larger trial will address weaknesses of the pilot trial via; modification of the intervention, increased power and follow up time, reduced severity of liver failure, increased generalizability of results due to multicentre setting and multiple CLD nurses.

# Study Objectives

## Primary Objective

To investigate changes in hospitalization rates associated with the intervention. Specific measures of hospital usage will include liver-related (unplanned and planned) admission and occupied bed day rates, all cause admission and occupied bed day rates, intensive care admission and occupied bed day rates and median length of stay.

## Secondary Objectives

- To evaluate incremental cost effectiveness for this intervention, relative to usual care. Assessment of quality of life will be a necessary component of the economic analysis. The QALY will be used to assess this outcome.
- To evaluate the effect of CDM on mortality
- To evaluate the effect of CDM on the quality of care provided to patients in the intervention arm. This will be assessed using the following measures:
  - attendance at planned outpatient care;
  - medication adherence;
  - adherence to antibiotic prophylaxis protocols for patients with ascites;
  - adherence to variceal bleeding prevention protocols;
  - adherence and response to alcohol abuse treatment protocols in alcoholic liver disease patients; and
  - referral rates to liver transplantation assessment teams.
- To compare self-management ability and knowledge of patients in the CDM arm with usual care models.

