## Outpatient review by Specialist Gastroenterologist/Hepatologist

Review by a specialist must be scheduled within 1 month (4 weeks) of discharge from hospital for all patients in the intervention group. The nurse must attend this appointment with the patient. In preparation for the outpatient appointment the following should be updated:

- - Medication list
  - Care Plan
  - Ensure screening and surveillance requirements are up to date (or booked)

At this appointment the specialist will discuss the care plan with the nurse and the patient and sign off on the care plan.

## Month 3, Month 6, Month 12, Month 18

Patients in the intervention group have their Child Pugh and Meld scores completed at 3, 6, 12, 18 months and at end of trial (Appendix N). Collect the information from the most recent bloods taken as part of usual care, the patient will not be required to have a blood test taken just for this score to be done.

Surveys are due for both groups at this time. For intervention patients this should ideally be scheduled at the same time the specialist outpatient appointment is scheduled to enable accurate determination of the Child Pugh and MELD score. Ensure the contact log is up to date. Patients will be provided the option of receiving the surveys via standard post or electronically, via email, at consent.

Record hospital and liver-related outpatient admissions/attendances/non attendances at the month 12 visit.

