## Quality of care indicators

Quality of care indicators, as outlined in the Aims section, will be measured. These indicators are recognized quality indicators ([44](#_ENREF_44)) and highly relevant process measures of successful implementation and effectiveness of the intervention. Attendances will include all planned outpatient medical, allied health, radiology and endoscopy appointments.

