## Data Monitoring

Outcome data for all endpoints will be monitored at 3-monthly intervals during the trial by the project team and at the trial midpoint to review adverse events, progress and preliminary outcome data.

Data will be submitted by scanning data collection records to the trial data manager. If a patient consents to receiving study surveys electronically, the CLD nurse involved in their care will send fillable surveys at each time point to the provided email address. The surveys will have the patient’s unique study ID allocated. Completed surveys will be emailed back to the CLD nurse, who will then check to ensure there is no identifying information recorded, before forwarding data on to the trial data manager as per standard process. All data will be saved in a secure password-protected computer for the duration of the study, which can only be accessed by the trial data manager.

| Activity Schedule for CONTROL patients | Baseline | Treatment Period  Day 7 to Week 11 are scheduled from the discharge date from hospital.  From Month 3 visits are scheduled from randomisation.  All visits/contacts have a window of +/- 2 days | | | | | | | | | | | | | | | | |
| --- | --- | --- | --- | --- | --- | --- | --- | --- | --- | --- | --- | --- | --- | --- | --- | --- | --- | --- |
|  | Baseline | Day 7 | Day 14 | Week  3 | Week  4 | Week  5 | Week  6 | Week  7 | Week  8 | Week  9 | Week  10 | Week  11 | Month  3 | Month  6 | Month  9 | Month  **12** | Month  18 | Month 24/EOS |
| Informed Consent | X |  |  |  |  |  |  |  |  |  |  |  |  |  |  |  |  |  |
| Child Pugh / MELD | X |  |  |  |  |  |  |  |  |  |  |  |  |  |  |  |  | X |
| SURVEYS (5) | X |  |  |  |  |  |  |  |  |  |  |  | X | X |  | X | X | X |
| Concomitant Medications | X |  |  |  |  |  |  |  |  |  |  |  |  |  |  |  |  | X |
| Comorbidities | X |  |  |  |  |  |  |  |  |  |  |  |  |  |  |  |  | X |
| Charlson Comorbidity Index | X |  |  |  |  |  |  |  |  |  |  |  |  |  |  |  |  |  |
| Randomisation | X |  |  |  |  |  |  |  |  |  |  |  |  |  |  |  |  |  |
| Cost/Resource use survey | X |  |  |  |  |  |  |  |  |  |  |  |  |  |  |  |  | X |
| Admissions to hospital |  |  |  |  |  |  |  |  |  |  |  |  |  |  |  | X |  | X |
| Liver-related appointments |  |  |  |  |  |  |  |  |  |  |  |  |  |  |  | X |  | X |
| Patient Satisfaction |  |  |  |  |  |  |  |  |  |  |  |  |  |  |  |  |  | X |
| Alcohol Use assessment |  |  |  |  |  |  |  |  |  |  |  |  |  |  |  |  |  | X |

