## Appendix K – Outpatient Attendance Log

Date of randomisation: ___ / ___ / ____

Period of review (tick only one):

Randomisation Date ___ / ___ / ____ to 12 months ___ / ___ / ____

12 months ___ / ___ / ____to trial end ___ / ___ / ____

| Outpatient review 1 |
| --- |
| Appointment Date ___ / ___ / ____  Attended? Yes  No  If no Why? Did not turn up  Cancelled |
| Outpatient review 2 |
| Appointment Date ___ / ___ / ____  Attended? Yes  No  If no Why? Did not turn up  Cancelled |
| Outpatient review 3 |
| Appointment Date ___ / ___ / ____  Attended? Yes  No  If no Why? Did not turn up  Cancelled |
| Outpatient review 4 |
| Appointment Date ___ / ___ / ____  Attended? Yes  No  If no Why? Did not turn up  Cancelled |
| Outpatient review 5 |
| Appointment Date ___ / ___ / ____  Attended? Yes  No  If no Why? Did not turn up  Cancelled |
| Outpatient review 6 |
| Appointment Date ___ / ___ / ____  Attended? Yes  No  If no Why? Did not turn up  Cancelled |

| Outpatient review 7 |
| --- |
| Appointment Date ___ / ___ / ____  Attended? Yes  No  If no Why? Did not turn up  Cancelled |
| Outpatient review 8 |
| Appointment Date ___ / ___ / ____  Attended? Yes  No  If no Why? Did not turn up  Cancelled |
| Outpatient review 9 |
| Appointment Date ___ / ___ / ____  Attended? Yes  No  If no Why? Did not turn up  Cancelled |
| Outpatient review 10 |
| Appointment Date ___ / ___ / ____  Attended? Yes  No  If no Why? Did not turn up  Cancelled |
| Outpatient review 11 |
| Appointment Date ___ / ___ / ____  Attended? Yes  No  If no Why? Did not turn up  Cancelled |
| Outpatient review 12 |
| Appointment Date ___ / ___ / ____  Attended? Yes  No  If no Why? Did not turn up  Cancelled |
| Outpatient review 13 |
| Appointment Date ___ / ___ / ____  Attended? Yes  No  If no Why? Did not turn up  Cancelled |

If more than 13 appointments in 12 months, please print this page a second time.

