## Appendix Q – End of Study Assessment Form

**To be completed on all patients (Intervention AND Control)**

| **Outcomes** | | **Yes** | **No** |
| --- | --- | --- | --- |
| 1 | Patient has **completed** the study (if yes complete table below)  Date of End of Study ____ / ____ / ______ |  |  |
| 2 | Patient has **DIED**  Date of Death ____ / ____ / ______ |  |  |
| 3 | Patient has been placed on the **transplant waiting list** (Complete below when placed on list)  Date of placement on waiting list ____ / ____ / ______ |  |  |
| 4 | Patient has been **LOST** to follow up  Date of last contact ____ / ____ / ______ |  |  |
| 5 | Date of Palliative Care Referral ____ / ____ / ______ |  |  |

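### Transplant-assessment referral, one of six quality-of-care measures, has no data field in either arm, and outpatient attendance is collected on a narrower scope than it is defined

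*Protocol*

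**What the plan says.** Secondary Objectives names six measures for the quality-of-care objective. The first is "attendance at planned outpatient care" and the last is "referral rates to liver transplantation assessment teams". Under Outcomes, the protocol commits to all of them: "Quality of care indicators, as outlined in the Aims section, will be measured". Statistical Methods then includes quality indicators among the outcomes whose between-group differences will be modelled.

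On transplantation, the only follow-up item is in the outcomes table of Appendix Q, completed for both arms: "Date of placement on waiting list". The End of Study section makes listing a reason for the final visit.

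On attendance, the Outcomes section sets the scope: "Attendances will include all planned outpatient medical, allied health, radiology and endoscopy appointments". The instruction for the month 3 to 18 visits is narrower: "Record hospital and liver-related outpatient admissions/attendances/non attendances at the month 12 visit". Both activity schedules carry a row headed "Liver-related appointments", ticked at month 12 and at month 24/end of study. Each entry in Appendix K reads: "Appointment Date ___ / ___ / ____ Attended? Yes No If no Why? Did not turn up Cancelled".

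**The concern.** A measure promised for comparison between arms needs a field that is filled in the same way in both arms. An analysis plan cannot supply a field that nobody recorded. For transplant referral there seems to be none. Waiting-list placement does not stand in for it, because a patient can be referred and then be declined, or die, without being listed.

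For attendance, the definition and the collection instruction describe different sets of appointments. A site following the visit instructions would leave out appointments that the definition counts. A site following the definition would log them, and nothing on the form would show which rule had been applied.

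The stakes are in interpretation. The protocol presents these indicators as process measures of whether the intervention was implemented and worked, so they would help explain either a null or a positive result on unplanned liver-related admissions.

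**Working it through.** No sample-size, power or event figure bears on this point, so the check is a match of each listed measure to the data-collection material shown: the visit text, the two activity schedules and Appendices A to U.

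| Measure (Secondary Objectives) | Where it is collected | Result |
|---|---|---|
| Outpatient attendance | Appendix K; month 3 to 18 text; schedule rows | Collected in both arms, narrower than defined |
| Medication adherence | ASK-12 survey | Covered |
| Antibiotic prophylaxis in ascites | Appendix C, prophylaxis item | Covered |
| Variceal bleeding prevention | Appendix F, adherence item at end of trial | Covered |
| Alcohol treatment | Appendix E items | Covered |
| Transplant-assessment referral | No field found | No data source |

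Count: 4 covered + 1 collected on a narrower scope + 1 with no field = 6.

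**Referral.**
- Appendix Q has waiting-list placement with its date, and a palliative care referral date, but no transplant referral item.
- Dietitian referral (Appendix G) and psychologist referral (Appendix E) have items. The gap is therefore specific to transplant referral and looks like an oversight.
- The care plan (Appendix S) could mention a referral in free text, but it belongs to the intervention and has no control equivalent.
- MBS and PBS data are given a costing role. The protocol does not name them as a source for referrals.

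**Attendance, side by side.**
- Definition (Outcomes): all planned outpatient appointments in four classes, with no liver-related limit.
- Visit text and both schedules: liver-related appointments only.
- End of Study section: the outpatient log is updated in both groups, with no limit stated.
- Appendix K: date, attended or not, and whether a missed appointment was a no-show or a cancellation. There is no type field and no liver-related limit on the form.

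The log therefore supports attended divided by planned for liver-related appointments in both arms. It does not support the same proportion over the full defined scope if sites follow the visit text. Nor does it allow the two scopes to be separated if sites differ.

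**Count or proportion.** The intervention arm has a specialist review due within 4 weeks of discharge, plus hepatologist clinics scheduled at months 3, 6, 12, 18 and 24: 1 + 5 = 6. The control schedule has no such row. Suppose controls have *n* planned appointments, intervention patients have *n + k*, and both attend with the same probability *p*. The ratio of attended counts is then (*n + k*)*p* / (*np*) = (*n + k*)/*n*, which exceeds 1 whenever *k* > 0. The ratio of attended proportions is *p*/*p* = 1. The protocol does not give *n*. Six is not *k* either, because usual-care patients keep their own clinics.

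**The case against.** Several points on the other side are sound.

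- **The log is not itself restricted.** Appendix K is a general outpatient log. The liver-related limit comes from the visit text and the schedule rows. This stands, and it makes the problem a conflict over scope between sections.
- **Attendance can be analysed.** A reader might infer that two of the six measures cannot be answered at all. The log gives attended out of planned in both arms, and neither the objective nor the definition asks for a breakdown by type. Only the measure on its defined scope is out of reach.
- **Attendance need not be biased.** A reader might infer that protocol-booked reviews inflate attendance in the intervention arm. That follows only for a raw count. Controls continue usual specialist care, better attendance is an intended effect, and the negative binomial model named for quality indicators does not rule out planned appointments as the denominator. An analysis plan may already settle this.
- **Mortality says little about missed referrals.** The background survival figures of 60% and 35% at two years imply 40% and 65% mortality, and a reader might infer that referral followed by death before listing will be common. Those figures are not a forecast for this trial, and the protocol gives no referral rate and no interval from referral to listing.
- **Referral may be recoverable.** Case notes could supply it, and some material (the randomisation page, fax templates, nurse checklists, data-entry screens) is not reproduced. This stands as a limit on the claim. But no section instructs anyone to abstract referral, so following the protocol as shown yields no such data.

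It could also be said that the objective speaks of care given to the intervention arm, so control data are not needed. Statistical Methods compares groups on quality indicators, and the intervention arm has no structured referral field either.

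**Conclusion.** The point holds in two parts of different weight. Transplant-assessment referral, one measure of six, has no data field in either arm on any form or schedule shown, and waiting-list placement is a later event that cannot replace it. Attendance, a second measure of six, is collected in both arms but cannot be derived on the scope the Outcomes section gives it. A proportion for liver-related appointments is available.

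Nothing here affects the primary outcome or its power. The conclusion rests on the forms and schedules reproduced in the protocol and would change if an unshown form carries a referral item. The documents do not allow the number of missed referrals, or any difference between arms in attendance, to be estimated.

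**What to change.** 1. Add to the outcomes table of Appendix Q, for all randomised patients in both arms including those who died: *Referred to liver transplant assessment team: yes/no, date*. Abstract it from case notes at the existing month 12 and end-of-study reviews. Patients already enrolled can be completed in the same way.
2. Choose one scope for attendance and use it in the Quality of care indicators section, the month 3 to 18 instructions and both schedule rows. If the wider scope is kept, add appointment type to Appendix K (liver clinic, other medical, allied health, radiology, endoscopy).
3. Compare attendance as attended out of planned appointments, not as a raw count, because the intervention schedule books specialist reviews that the control schedule does not. If the analysis plan already says so, no change is needed on this item.

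The cost is one form item, possibly a second, a wording alignment and a small amount of extra abstraction time. Keeping the wider attendance scope costs more abstraction than narrowing the definition to liver-related appointments.
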